**Figure 1 fig1:**
[figure not shown]
Study design with timeline.

In the pre-pilot phase, caregivers will be contacted by researchers and screened by phone according to the inclusion criteria (see par 2.2.1.). If the recruited person meets the inclusion criteria, they are included in the sample and they receive the online questionnaires (see Appendix 1) and the informed consent. Contextually, during the phone call, the researcher and the interviewee agree to a face-to-face meeting during which the informed consent is given back signed to the researcher. The latter asks for the possibility of also speaking with the older care recipient, if they are able to answer a very brief interview. Between the screening and the T0 the researcher receives and reads the questionnaire compiled online by the caregiver. At the baseline (T0), the researcher administers the face-to-face interview (see Appendix 2) starting from the answers that the caregiver gave to the questionnaire. When it is possible also the care receiver is interviewed. In the intermediate phase (T1), caregivers and body–mind trainers are briefly interviewed with the aim of understanding whether the activities are liked and effective and whether adjustments need to be made. In the post-intervention phase (T2), the caregivers are asked to answer the questionnaire (containing the same dimensions explored in T0 except for the socio-demographic data) and to participate in a second interview. In this phase, the 15 older adults are interviewed again.

### Sample size, recruitment strategy and inclusion criteria

2.2

The study aims to reach a total of 30 informal (i.e., relatives, friends, neighbors) and semi-formal caregivers (i.e., migrant family care assistant) and 15 older care receivers per country (total 90 caregivers and 45 older adults), without internal stratification considering the very low number of participants. The study is exploratory and is designed to generate in-depth insights into participants’ experiences rather than to test predefined hypotheses. Accordingly, no formal *a priori* power calculation was conducted, because the sample is intended to provide sufficient informational richness (i.e., “information power”) to address the research aims, rather than statistical representativeness. The sample size was decided upon because the few studies on the effects of dance-based interventions have included samples of this scale (Marmeleira et al., 2009), and others based on the use of multiple artistic mediums such as drawing and music involved approximately 20 subjects (McCarthy et al., 2019; Malyn et al., 2020). Furthermore, given that DanceCARE sample is representative for meaning and not statistically representative (Luborsky and Rubinstein, 1995), a study of the statistical power of the sample is not planned (Jones et al., 2003). Feasibility considerations, including recruitment capacity, available resources, and the intensity of the intervention, further informed the target sample size. To account for potential attrition, a dropout rate of approximately 10–15% has been anticipated, and recruitment will be adjusted accordingly where possible. Participant retention will be monitored throughout the study.

Informal and semi-formal caregivers are recruited using the snowballing method (Valerio et al., 2016), through word of mouth and by spreading leaflets in general practitioners’ ambulatories, geriatric hospitals, territorial health and social services, gyms, pharmacies, voluntary and caregivers’ associations, and through social media, i.e., Facebook and piloting organizations’ websites.

In the three pilot sites in Greece, Italy and Spain, informal caregivers are included if they provide care for an older (65+) family member by choice and/or necessity, without any kind of remuneration for at least 1 year and if they provide at least 12 h of care per week; with a stress self-assessment > of 5 on the stress scale, and if they agree to participate by signing the informed consent. Migrant family care assistants are enrolled if they have been caring for at least 1 year and for at least 20 h per week (Fisher et al., 2021) with a stress self-assessment > of 5 on the stress scale (question no. 8, Caregiver and Supported Person Screening Questionnaire) and if they agree to participate by signing the informed consent. To determine the number of hours, excluding those who live with the person they care for, we relied on recent sector-specific studies that indicate a wide range, with an average that often hovers around 20 h per week for those providing semi-formal care to older people (Verbakel, 2018).

Many informal caregivers are considered “intensive” caregivers when they provide 11 or more hours of care per week. Older adults with long-term care needs are enrolled if they are aged 65 years and over (both men and women); if they have a score on the IADL scale (Lawton and Brody, 1969) between 4 and 6 (indicating an average level of dependency which, however, does not preclude the ability to answer the questions of the questionnaire) and if they agree to participate by signing the informed consent. No other socio-demographic criteria are adopted for selecting participants (see Table 1).

**Table 1 tab1:** Participants’ selection criteria.

Type of participants	Inclusion criteria	Exclusion criteria
Informal caregivers	– To provide care for an older family member by choice and/or necessity, without any kind of remuneration	– Receiving payment for caregiving
	– To be aged more than 18 years	– To be aged less than 18 years
	– To be involved in the caring task for at least 1 year	– To be involved in caring tasks for less than 1 year
	– >12 caring hours/week	– <12 caring hours/week
	– To have a self-assessment of stress ≥5 on a ladder from 0 to 10	– To have a self-assessment of stress <5 on a ladder from 0 to 10
Semi-formal caregivers	– To carry out care work in close contact with the family members of the older person being cared for	
	– Migrant care workers, social workers, family assistants, live-in caregivers	
	– To be aged >18 years	– To be aged <18 years
	– To be involved in the caring task for at least 1 year and for ≥12 h/week	– To be involved in caring tasks for less than 1 year and for <12 h/week
	– To be involved in the caring tasks ≥20 h/week	– To be involved in the caring tasks <20 h/week
	– To have a self-assessment of stress ≥5 on a ladder from 0 to 10	– To have a self-assessment of stress <5 on a ladder from 0 to 10
Older people with LTC needs	– People aged 65 and over	– Multi-morbid conditions must not have seriously impaired their cognition and ability to answer short questions

### The DanceCARE intervention

2.3

The development of the intervention called “Body-mind education for stress relief”, and the use of specific body–mind techniques was defined through the results of an online survey among 140 European dance movement therapists, followed by a focus-group involving 10 experts in the field of art-based interventions and care-giving, e.g., body–mind therapists, LTC researchers and psychologists. To support the development of the program, a literature review was also conducted on the emotional needs and soft skills that caregivers of older adults should develop to cope with stress. Based on these results, seven body–mind group sessions were developed by the EADMT and WM team together, with the support of the Coordinator, which was an enriching learning exchange for both teams. The EADMT team also involved [name], as an external advisor on DMT, dementia and LTC, to take a look at the draft training program, and give suggestions for improvement.

Specific guidelines have been developed for body–mind trainers, and translated in Italian, Greek and Spanish, containing basic instructions for the proper facilitation and management of small groups, details regarding the structure and duration of each individual workshop, and preparation of the setting. The guide then goes into detail about each session of the educational program, clearly explaining for each one what the central theme is and what needs it addresses, how the workshop unfolds, and the body–mind techniques suggested. The explanation of the sessions provides description and indications for users to understand the body work and the exercises proposed.

Sessions one, three and seven were structured more according to the WM method, and the rest were fully based on DMT approach in order to form a multi-modal progressive “body–mind” intervention. The overall set up and structure of all sessions and the therapeutic embedding followed the European DMT guidelines. The program puts into practice seven group sessions (Table 2), some of which utilize neuroscientific knowledge in calming down the body and others enhanced emotional and/or creative expression. Where deemed appropriate for the conduct of the session, possible materials and music tracks are also suggested for each session of the intervention, with links, and a description of the development of the practice and the proposed creative and body work is included. Furthermore, since this is a blended programme, for each session there is a link to a video tutorial on the DanceCARE YouTube channel to complement the in-person session. The video provides more detail on the exercises and reinforces the proposed practices and encourages you to continue moving at home.

**Table 2 tab2:** Short description of the DanceCARE intervention.

Sessions	Subject	Key take away
Session 1	Self-awareness: breathing, grounding and slowing down	Through slow breathing, you can calm down your nervous system.
Session 2	Self-confidence, body posture, mobility	Growing awareness of self on a physical and emotional level. Expanding their toolbox, with tools for selfcare. Processing information by improvising individual dance and developing their own choreography.
Session 3	Mindfulness and the surroundings (stress-management)	Being in nature, and imagining nature, releases stress
Session 4	Empathy (inwards and outwards empathy) and resilience (self-care practices)	Attunement, a base for empathy and communication.
Session 5	Emotional regulation (coping strategies)	Embodying difficult moments, give them a place to be expressed, observe them and try to deal with them through creativity.
Session 6	Communication skills, expression and listening (embodied, non-verbal and verbal communication)	We encourage elements such as trust, cooperation and openness to creativity, to achieve greater awareness of emotions and new forms of personal and social expression.
Session 7	Social interaction and creativity	You can create a connection and a pleasant, shared experience with someone, like the one you care for, through drawing, singing or dancing together.

Prior to the pilot phase, a small group of professionals—comprising two or three representatives from each country involved in the pilot project (hereinafter referred to as “mind–body trainers”)—will undergo specialized training, based on the aforementioned guidelines, on the intervention to be carried out with informal and semi-formal caregivers. All body–mind trainers have a background in DMT and are licensed through an institution recognized by the European Association of Dance Movement Therapy. All selected DMT trainers have on average over 5 years of work experience and are registered with national dance therapy associations.

Also, to ensure effective monitoring, each session will be attended by an observer—either a therapist specializing in DMT or a trainee selected at the national level through relevant associations and institutions. The observer will be provided with project guidelines, previously translated in the national language, for observing the body–mind sessions, thereby contributing to the collection of high-quality art-based and embodied material.

The intervention for the caregivers consists of 1 h and a half weekly face-to-face activities based on the DMT and WM techniques previously identified and developed in group for stimulating communication and peer networking, thereby counteracting isolation and the exacerbation of stress and other symptoms such as depression (Lauritzen et al., 2015). The frequency of the body–mind sessions has been defined during the construction phase of the programme through expert advice, but also through the collection of opinions of the caregivers themselves.

As shown in Figure 2, at each of the three pilot sites, 30 informal caregivers will be divided into three groups of up to ten participants, who will attend the program simultaneously on different days and at different times of the week for approximately 3 months, taking into account holidays and other factors that could slightly affect the timeline.

**Figure 2 fig2:**
[figure not shown]
Participants’ flowchart.

The in-person activities are supplemented by online activities through nine video lessons translated into the languages of the project and based on the DanceCARE method, available on a YouTube channel^3^ and by an online platform that also includes a chat where the participants to the intervention can keep in touch between a session and another, sharing feelings and observations on their experience within the intervention.

### Outcome variables and research tools

2.4

Employing a mixed-method design, this study will collect data on both quantitative and qualitative outcome variables, explored through proper data collection tools, at three time points (T0–T1–T2).

Table 3 provides an overview of all outcome variables, measures and research tools by target group and data collection waves. In the following two sub-paragraph quantitative and qualitative research tools are deepened.

**Table 3 tab3:** Outcomes variables and tools by target group and data collection time.

Target group	Method	Variables	Tools	Time
Informal and semi-formal caregivers of older adults Older care takers with LTC needs	Quantitative	Variables for the assessment	Common assessment tool	Screening
		Level of stress load	Zarit Burden Interview (ZBI)	T0 and T2
		Dimensions of burden	Caregiver Burden Inventory (CBI)	T0 and T2
		Depression	Beck Depression Inventory (BDI)	T0 and T2
		Satisfaction with the intervention	*Ad hoc* Likert scale-based questions	T1 and T2
	Qualitative	Personal experience with caregiving	*Ad-hoc semi-structured interview*	T0 and T2
		How and why they experience the level of stress and burden referred in the questionnaire		T0 and T2
		Perceived change of stress		T0 and T2
		*Mid-term short evaluation*: Suggestions and opinions regarding the intervention and the online learning platform and chat		T1 and T2
		Self-reflection on the body–mind experience	*Self-observation diary* for the caregivers	longitudinal
	Quantitative	Perceived quality of life	Ad hoc Likert scale-based question	T0 and T2
		Satisfaction with the care received	Yes/no and open-ended questions	T0 and T2
	Qualitative	Perceived care received	Open-ended question	T0 and T2
Body–mind trainers	Qualitative	Reporting on the body–mind sessions	*Reporting guide*	Over the intervention
		*Mid-term short evaluation*: Suggestions for improving the intervention, the online platform use and observed reactions in caregivers	Open-ended question	T1

The tools chosen in the design of this pre-post study to assess depression and psychological distress are validated versions for each country involved in the piloting. They will be sent to participants via online forms for self-administration. In addition, all interviews will be recorded and transcribed initially at the national level and then translated into English to enable a transnational analysis of the data.

For the qualitative monitoring conducted over the duration of the body–mind programme, the observers will provide data via online forms in which, in addition to noting a range of aspects of movement and dynamics in written form, they are also able to attach art-based and/or embodied materials consisting of images and/or videos relating to each individual group session. Importantly, these qualitative data will not be limited to verbal accounts; they will also include symbolic and metaphorical expressions emerging from arts-based and embodied practices, which remain grounded within the qualitative paradigm and allow for a process-oriented understanding of participants’ experiences rather than capturing them at a single point in time.

For data collection, the implementation of rigorous protocols is prioritized, and researchers are provided with detailed guidelines to minimize inter-observer variability.

A triangulation strategy will be employed using multiple data sources (e.g., tests, interviews, and observations) to validate the results.

A mid-term review will also be conducted with both participants and body–mind trainers to ensure accuracy of the study’s interpretation.

Finally, a reflexive approach is adopted to reduce researcher bias and potential prejudices in the qualitative analysis.

#### Quantitative variables

2.4.1

Feasibility will be evaluated using predefined indicators, including recruitment rate, retention and attrition, adherence to the intervention, and completeness of data collection. Acceptability will be assessed through participant feedback. These parameters will be summarized descriptively to inform the practicality and optimization of the study design.

Concerning the assessment of the impact of the intervention on participants, the primary outcome variables are caregivers’ burden measured using, respectively, the ZBI (Zarit et al., 1987, 1980; Chattat et al., 2011) and the CBI (Novak and Guest, 1989; Valer et al., 2015). The researchers further investigate the aspect of depressive state through the BDI (Beck et al., 1961). These are self-assessment, standardized psychometric instruments, in the form of questionnaires, which can be self-completed by the subjects. It was decided to use two tests to measure caregivers’ burden because the ZBI identifies the consequences of care-giving on the caregiver’s quality of life and psychological and social condition in general, while the CBI delves deeper into the dimensions related to specific individual areas of burden, i.e., objective, psychological, physical, social, and emotional burden.

The ZBI is the most widely used instrument. Originally designed and tested in 1980, it contains 22 questions. Its brevity allows for easy administration and requires the caregiver to respond via a 5-point Likert scale from 0 (never) to 4 (almost always) according to the degree of agreement they have with the individual items. The items investigate how the patient’s disability impacts the quality of life, psychological discomfort, guilt, financial difficulties, shame and social and family difficulties of the caregiver. Consequently, the total score, which is calculated by summing the individual item response scores, is between 0 which corresponds to no care burden, to a maximum of 88 which corresponds to a maximum level of care load. Values between 21 and 40 indicate a light to moderate care burden. Values between 41 and 60 indicate a moderate to severe care burden. Values between 61 and 88 indicate a severe care burden. Scores above 24–26 identify caregivers for whom further investigation and possible support interventions would be indicated (Schreiner et al., 2006).

The CBI is a care burden assessment tool, capable of analyzing the multidimensional aspect, especially developed for caregivers of patients suffering from Alzheimer’s disease and related dementias. It is a self-report instrument, filled in by the main caregiver, i.e., the family member or caregiver who most bears the burden of caring for the patient. The caregiver is asked to answer by ticking the box that comes closest to his/her personal condition or impression. It consists of 24 items divided into five sections, i.e., objective burden, psychological burden, physical burden, social burden and emotional burden. The CBI allows different stress factors to be assessed: the time-dependent burden of care (item 1–5), which describes the burden associated with the restriction of time for the caregiver; the developmental burden (item 6–10), understood as the caregiver’s perception of feeling cut off, compared to the expectations and opportunities of their peers; the physical burden (items 11–14), which describes feelings of chronic fatigue and somatic health problems; the social burden (items 15–19), which describes the perception of role conflict; the emotional burden (items 20–24), which describes feelings towards the patient, which may be induced by unpredictable and bizarre behavior. The items are rated on a Likert scale from 0 to 4, with a minimum score of 0 and a maximum score of 96, where a higher score represents a greater burden on the caregiver. The CBI makes it possible to obtain a graphical profile of the caregiver’s burden in the various domains, to compare different subjects and to immediately observe changes in burden over time. Caregivers with the same total score may present different burden patterns. These disparate profiles address the particular social and psychological needs of caregivers and represent the different objectives of assorted intervention methods planned to relieve the specific weaknesses specified in the test. The lowest test reliability is found regarding emotional and social burden. Although no specific values have been established for the CBI, according to the Minimal Clinically Important Difference (MCID) parameters (McGlothlin and Lewis, 2014; Salas Apaza et al., 2021), a 10–20% reduction in the total score is often considered significant in similar load measures.

The results that emerge are not to be considered exhaustive for caregiver’s emotional health status, that’s why the researchers decided to do an integration of measurements concerning specifically depressive aspects through BDI.

BDI is used as a screening tool for depression and to measure behavioral manifestations and severity of depression. Validity and reliability for BDI have been tested across populations, worldwide. It can be used from ages 13 to 80 and contains 21 self-report items which individuals complete using multiple choice response formats. The BDI score ranges from 0 (no symptoms of depression) to 63 (maximum depression). Scores above 40 already indicate extreme depression. Research indicates that a 17.5% change in the BDI score from baseline indicates a clinically significant change (Button et al., 2015).

Secondary quantitative outcomes are: the degree of satisfaction of caregivers with the intervention, assessed with ad-hoc closed and open questions; the quality of life perceived by the care takers, measured with a single question that can be answered with a score from 1 to 5, where 1 is “very good” and 5 is “very bad”; the care takers’ satisfaction with the care received, measured using a yes/no question and an open-ended question to provide explanations for their answer.

Considering the quantitative instruments, the screening questionnaire collects the socio-demographic data of the caregivers and information on the type and frequency of care provided, for the purpose of inclusion or non-inclusion in the study. It also includes questions about the willingness to attend the activities offered within the intervention and the expectations the caregivers have of it, in order to be able to adapt the activities as much as possible to the needs of the participants. The screening questionnaire evaluates the older person’s abilities to understand and answer the questionnaire by means of the Lawton Instrumental Activities of Daily Living (IADL) scale (Lawton and Brody, 1969) answered by the caregiver.

The questionnaire administered to caregivers before and after the intervention (at T0 and T2) contains the ZBI, the CBI and the BDI, as described above.

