### Study design

2.1

The main aim of the study is to examine the feasibility of the innovative, blended, and flexible educational program based on DMT and WM methodologies. The second aim is to check if and how the application of key body–mind methodologies contribute to the reduction of burden, depression and isolation of informal and semi-formal caregivers, and at the same time to the increase of the quality of life of older care takers. The study wants to answer the following main research questions “Is the DanceCARE intervention feasible to implement in terms of recruitment, retention, adherence, and acceptability?” and “To what extent and how can the DanceCARE intervention change the perceived burden and depression levels of semi-formal and informal caregivers of older people with long-term care needs?”

Other research questions include whether the intervention also improves the quality of life of the older person receiving care, and whether the blended approach—which involves support through short online videos—is considered helpful and effective by the participants.

To answer these questions, this pilot convergent mixed-method study, chosen in preparation of a future full-scale study, integrates standardized quantitative instruments for measuring perceived levels of burden and depression, with diverse qualitative approaches to capture the complexity of human experience, e.g., interviews, focus-groups and live observations of participants during the body–mind sessions, enriched by art-based and embodied research approach (Hervey, 2000).

These qualitative data will not be limited to verbal accounts; they will also include symbolic and metaphorical expressions emerging from arts-based and embodied practices, which remain grounded within the qualitative paradigm and allow for a process-oriented understanding of participants’ experiences rather than capturing them at a single point in time.

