In accordance with the intention-to-treat (ITT) principle, participants who withdraw from the study will not be replaced. Missing data in co-variates will be handled using multiple imputations via chained equations. All statistical analyses will be conducted by a statistician blinded to group allocation. A significance level of *p* < 0.05 will be used throughout. Analyses will be performed using SPSS for Windows, version 24.0 (SPSS Inc., Chicago, IL, USA).

Qualitative data are analyzed thematically following Braun and Clarke’s (2006) approach. Two independent researchers will analyze the textual data, with a third reviewer verifying the results to ensure reliability (Golafshani, 2003; Lincoln and Guba, 1985; Shenton, 2004). Observational notes, reports (and, when shared, also the diaries written by caregivers) will be compiled into narratives and then summarized across countries (Kutsche, 1998). These narratives will be coded to highlight information relevant to the research questions. The resulting codes will be grouped into overarching themes (De Munck and Sobo, 1998). To minimize subjective bias, the coding process will again be performed by two independent researchers and reviewed by a third (Golafshani, 2003).

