### Study limitations, challenges and strengths

3.3

In this mixed-method study, bias can emerge from the quantitative component (e.g., randomization failures), the qualitative component (e.g., researcher subjectivity), or the integration of both. Common sources include selection bias (unrepresentative samples), measurement bias (inaccurate tools), and expectancy bias (researcher/participant preconceived notions). Given the meaning-based sampling procedure and the absence of a control group, we planned to mitigate potential biases by using various quantitative measures and combining them with qualitative data.

In particular, the proposed study presents some limitations and potential challenges that must be acknowledged. First, the recruitment process may prove demanding, as informal caregivers often face multiple constraints such as lack of time, physical exhaustion, emotional overload, transportation difficulties, and competing family responsibilities. These factors, combined with possible reluctance to participate due to privacy concerns or fear of being judged on their caregiving and/or movement abilities, may hinder enrolment. Furthermore, since recruitment largely depends on community networks and voluntary participation, there is a risk of selection bias toward caregivers who are already motivated or have more flexible schedules, which may limit the representativeness of the sample. Another challenge concerns participants’ adherence throughout the intervention. Given the vulnerability and daily burden of informal caregivers, dropouts may occur due to health deterioration, caregiving crises, or changing family circumstances.

Additionally, the small sample size and the pilot nature of the study limit the generalizability of the results. The qualitative data collection while providing deep insights may also be influenced by cultural and linguistic differences across the three participating countries, as well as by participants’ varying levels of comfort with embodied or art-based expression. Finally, although measures have been taken to standardize the protocol across pilot sites, differences in facilitation styles among DMT and WM trainers could introduce variability in intervention delivery.

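### The plan claims allocation blinding and cites randomisation bias in a single-group study, disclaims hypothesis testing yet sets p<0.05 throughout, and gives its yes/no feasibility aim no stated reading

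*Protocol article*

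**What the plan says.** All references are to the Protocol article.

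- **Aim.** Section 2.1 states: "The main aim of the study is to examine the feasibility of the innovative, blended, and flexible educational program". Effects on burden and depression are the second aim. The first research question is "Is the DanceCARE intervention feasible to implement in terms of recruitment, retention, adherence, and acceptability", and the design was "chosen in preparation of a future full-scale study".
- **Feasibility analysis.** Section 2.4.1: "Feasibility will be evaluated using predefined indicators, including recruitment rate, retention and attrition, adherence to the intervention, and completeness of data collection". Acceptability comes from participant feedback. Then: "These parameters will be summarized descriptively to inform the practicality and optimization of the study design".
- **Feasibility figures.** Section 2.2 gives a target of 30 caregivers per country (90 in all) and an anticipated dropout of 10–15%, with retention monitored. No consequence is attached to either figure.
- **Testing.** Section 2.2 says the study is meant to give insight into experience "rather than to test predefined hypotheses", and there is no power calculation. Section 2.5 plans paired t-tests of T0 against T2 and a 0.05 level for every analysis. It considers multivariate models only where the univariate result is significant.
- **Expected changes.** Section 3.2 expects a fall of at least 10 points on the ZBI, 10–20% on the CBI and 17.5% on the BDI.
- **Comparative wording.** Section 2.5: "All statistical analyses will be conducted by a statistician blinded to group allocation". Section 3.3: "bias can emerge from the quantitative component (e.g., randomization failures". Both sections also say there is no control group, and Section 2.5 accepts that causal conclusions cannot be drawn.

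**The concern.** There are three faults of unequal weight.

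First, two phrases belong to a randomised comparison. With one group there is no allocation to be blind to and no randomisation to fail. A reader could credit the analysis with a protection it does not have. Meanwhile the biases that do threaten a pre-post comparison in people selected for stress go unnamed.

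Second, a study that says it does not test hypotheses applies a significance threshold everywhere and lets it decide whether further models are fitted. The threshold answers whether change differs from zero. Without a control group, and with expectations stated as sizes of change, that is not the useful question.

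Third, the main question calls for a yes or a no, but the stated analysis is description alone. High and low retention would be handled in the same way, and the judgement would be made after the figures are known.

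**Working it through.** **1. Allocation wording.** Set side by side, Section 2.5 has a statistician blind to allocation and, in the same section, no control group. Section 3.3 has failed randomisation as an example of bias and, in the same paragraph, no control group. The statements cannot both apply. The biases that do apply follow from the plan itself:

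- Entry requires a stress self-rating of about 5 or more out of 10 (the Section 2.2 text says above 5, Table 1 says 5 or above), so some regression to the mean is plausible.
- T0 is 3 months before training starts and the programme lasts about 3 months, so T0 to T2 spans about 3 + 3 = 6 months of possible drift.

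**2. What p<0.05 would detect.** The plan has no power figure to reproduce. Inputs are n = 90 (no loss) down to n = 77 (about 15% loss), with a two-sided test assumed. The smallest significant standardised change is t(0.975, n−1)/√n:

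- n = 90: 0.209
- n = 77: 0.227

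The SD of ZBI change is not in the document. Over an assumed range of 8 to 15 points, the smallest significant fall runs from 0.209 × 8 = 1.7 to 0.227 × 15 = 3.4 points, against the 10 points expected in Section 3.2. An uncontrolled drift of 0.3 SD would be declared significant with probability 0.74 (n = 77) to 0.80 (n = 90).

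**3. The plan's own retention figures.** 90 × 0.90 = 81 and 90 × 0.85 = 76.5, so 77 is the smallest whole number that reaches 85%. Wilson 95% intervals, [p + z²/2n ± z√(p(1−p)/n + z²/4n²)]/(1 + z²/n) with z = 1.96, are:

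- 77/90 = 85.6%: 76.8% to 91.4%
- 26/30 at one site = 86.7%: 70.3% to 94.7%

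The pooled figure is usable. A single site's figure is too wide to carry a rule alone.

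**4. Can 90 participants support a retention rule?** Exact binomial, P(X ≥ k) = Σ C(90, x) pˣ(1−p)⁹⁰⁻ˣ for x from k to 90:

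| Cut | True 70% | True 85% |
|---|---|---|
| at least 77 of 90 | 0.00 | 0.51 |
| at least 71 of 90 | 0.04 | 0.96 |

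Putting the cut at the planned rate fails a study that performs to plan about half the time. A cut at 71 of 90 (78.9%) separates 85% from 70% well. The 70% comparator is an illustration and does not come from the document.

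**The case against.** The strongest reply is that this is a condensed article. Descriptive reporting of feasibility is normal in a pilot, the indicators are called predefined, and cut-offs may sit in a fuller protocol or analysis plan. That largely stands against any complaint about a missing number. It does not remove the mismatch within this text, which poses a yes/no question and then commits its answer to description only.

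Several stronger readings are tempting and are not supported:

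- *Burden has displaced feasibility as the primary outcome.* Section 2.4.1 calls burden primary only within the assessment of impact on participants. Sections 2.1 and 2.5 both keep feasibility first.
- *The Section 3.2 marks are tested at p<0.05.* They are not. The paired tests are against zero change, and no analysis is tied to those marks.
- *The plan has no feasibility figures.* Section 2.2 gives a recruitment target and a dropout range.
- *The full-scale decision would rest on pre-post changes.* No passage says so, and causal conclusions are expressly disclaimed.
- *The first question can never be answered no.* Poor recruitment or retention, once described, could still be judged infeasible. What is missing is a reading fixed in advance.

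It is also fair that the absence of a control group is stated openly, which limits the harm of the leftover wording, and that effect sizes are already planned beside p-values.

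**Conclusion.** The point holds in a limited form. The allocation-blinding statement is wrong on its face, and the randomisation example does not fit the design. The 0.05 threshold conflicts with the disclaimer of hypothesis testing, and it would flag ZBI changes of roughly 2 to 3 points where 10 are expected (SD of change assumed to be 8 to 15). The main aim lacks a stated reading, although 90 participants are enough to support one for retention. The probabilities assume 90 enrolled and independent retention; dropout that clusters within the session groups would make them less favourable. None of this undermines the study as a descriptive pilot. It should be corrected because the changes are cheap and a feasibility reading is credible only if it is fixed beforehand.

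**What to change.** 1. **Section 2.5:** delete the statement on blinding to allocation. **Section 3.3:** replace the randomisation example with regression to the mean after selection on stress, and drift over the T0–T2 interval.
2. **Section 2.5:** report T0–T2 change in ZBI, CBI and BDI as mean change with 95% CI, read as exploratory against the Section 3.2 expectations. Drop 0.05 as a criterion, including as the trigger for multivariate models.
3. **Section 2.4.1:** before T2 data are seen, state a sponsor-chosen proceed/modify/stop reading for recruitment, retention, adherence and data completeness, each with its denominator and a 95% CI. Use the plan's own 30 per site and 10–15% dropout as the reference. Recruitment counts are known earlier, so that reading should be fixed correspondingly earlier. If a fuller protocol already holds such criteria, cite them.
4. **Retention:** choose a pooled rule that a study performing to plan would usually pass. At least 71 of 90 is an illustration, not a recommendation. Avoid a single cut at 77 of 90.

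The cost is wording in the protocol and analysis plan, with no extra participants or data. The downside is that the study can then fail its main aim.
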